# Background and rationale for study

Maternal mortality in Sierra Leone is one of the highest globally (1,360 deaths per 100,000 live births in 2015)^1^ with teenage pregnancy a leading cause of death for mothers; teenage mothers are 40-60% more likely to die during childbirth.^2^ However due to ineffective maternal death reporting, this could be significantly higher. A household survey conducted in 2015 indicated a maternal death rate of 1 in 10 for under-18-year-olds in Eastern Freetown. A following study examined the causes of this high incidence of maternal death in teenagers and highlighted intersecting health and socio-economic vulnerabilities.^3^ Among key findings were that pregnant teenagers are often neglected by their families, particularly when being cared for by a non-parental adult, often sleeping on bare ground without a mosquito net, and are fed once a day in exchange for heavy domestic duties such as water collection and laundering, in many cases with little protection from ongoing gender-based violence. This lack of adult care or support often leads to delays in care-seeking or complete lack of antenatal and delivery care, putting teenagers at high risk of death from undetected pre-eclampsia, untreated infections, anaemia, lack of birth preparation, and common obstetric risks.^3^ To achieve the Sustainable Development Goals target of reducing the maternal mortality rate to less than 70 per 100 000 live births by 2030, adolescent girls are a priority group. ^4-6^

These findings led to the development of 2 Young Lives (2YL), a locally-designed intervention that provides mentoring from pregnancy through to one-year post-birth for women aged under-18. This encourages mentees to take up antenatal care and hospital birth, re-establish family connections where this is safe and appropriate, promotes health-seeking behaviour, provides practical advice about childbirth, parenting and contraception, and supports mentees to return to education or start vocational training. The 2YL scheme was piloted in 2017/2018 in an urban suburb of the capital, Freetown, and expanded to new sites in 2018, 2019 and 2021.^7^

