# Study objectives

Primary objective

To determine whether a pilot trial of the 2YL mentorship scheme for pregnant teenagers is feasible and to inform a future larger trial to evaluate the effectiveness of 2YL in improving pregnancy outcomes for mothers and babies in Sierra Leone.

Secondary objectives

To assess the integrity of study protocol including: recruitment, randomization procedure, data collection, retention and follow-up procedures, acceptability of intervention, primary outcome measure and sample size calculation, refinement of the intervention and training and supervision procedures, and estimation of resource use and costs.

To assess health, social, educational and economic outcomes of the 2YL intervention for young mothers and babies

To explore experiences, mentoring and thriving among young women receiving the 2YL intervention compared to those receiving usual care.

To evaluate the implementation, context and mechanisms of change of the 2YL intervention in order to understand the results and its potential impact.

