Both quantitative and qualitative data on processes and implementation will be collected from monthly checklists, separate focus groups with a purposive sample of mentors, PHU healthcare staff and other community stakeholders such as teachers and community elders (n≈4), and semi-structured interviews with young women in control and intervention sites (n≈40). If appropiate, a family member or a friend will also be invited to participate in an interview. Women will be offered the opportunity to be one-to-one (interviewer and participant) or one-to-two (interviewer and participant with chosen family members/friend). Thus, if appropriate, family member/friend can be invited to the interviews as social support is culturally patterned and could play an important part in the mechanisms of the intervention, particularly in women’s engagement with care. Interview administered wellbeing measures will include, for example, PHQ-9, the flourishing scale for adolescents, women’s empowerment scale. A small sub-group of participants (n≈6-10) will also be invited to take part in the photovoice pilot project^18^.

Considering how different contexts may affect implementation, as well as the intervention itself, will allow a flexible approach to future scaling up based on this understanding. The following table indicates possible research questions which will be refined in forthcoming stakeholder workshops and will be discussed in focus groups discussions and interviews:

| Context item | Possible interaction with implementation | Specific examples |
| --- | --- | --- |
| Geographical | Rural vs urban settings?  Seasonality – how do the seasons impact on the implementation of 2YL. | In rural settings, how are mentees supported with small business option when there is no local market?  Do monthly gatherings still take place in the rainy season?  Can mentoring mitigate the 2^nd^ delay when roads are impassable in the rainy season? |
| Socio-cultural | Family make-up: living with birth parents / relatives; married (child marriage) vs unmarried  Tribal, religious, ethnic norms and beliefs | Where child marriage is common, how does being married impact on the empowerment 2YL confers?  Is there a reluctance from husbands for married girls to enrol in 2YL? How can this be overcome?  Are there characteristics of tribal, ethnic and religious groups that impact on the acceptability of 2YL? (Various elements such as business, education, contraception) |

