**-** For young women and their families where there is no assumption of literacy, a verbal explanation of the study will be provided in Krio or other local language, and give out information sheets which will be pre-tested. Consent will be sought at the start of all interviews and focus groups, with the information sheet being explained again, with opportunity for questions. For participants under 16, written consent will be sought from their parent or guardian where possible, using a personal approach by the research assistant to explain the research and the information sheet. Assent will be sought from the under 16-year-olds.

All participants being asked to provide personal sensitive data will be asked to give explicit consent for the collection and use of such data using the standard wording of the Data Protection Act statement. Participants will be fully informed on the Information Sheet of the intention to re-use or retain data for purposes other than the trial report, e.g. journal articles. Participants will be given the opportunity to withdraw from participation at any point both during the data collection and for up to four weeks following data collection.

Where eligible participants are present prior to a focus group starting (e.g., by a girl bringing an eligible friend along), consent will take place just prior to the focus group on the grounds that bringing the participant back on another occasion may disadvantage the participant economically or educationally.

Mitigating risks to participants

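### The wellbeing scales may be completed with a family member or friend in the interview, and the protocol neither requires privacy nor records who was present

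*Protocol*

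**What the plan says.** Four parts of the protocol bear on this point.

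- **Data collection, Process Evaluation.** The plan is for "semi-structured interviews with young women in control and intervention sites (n≈40". On format it says "Women will be offered the opportunity to be one-to-one (interviewer and participant) or one-to-two (interviewer and participant with chosen family members/friend". The companion is more than an observer: "a family member or a friend will also be invited to participate in an interview", subject to this being appropriate, with no criterion given. Two sentences after the choice of format comes "Interview administered wellbeing measures will include, for example, PHQ-9, the flourishing scale for adolescents", with an empowerment scale as a further example.
- **Ethical considerations.** The consent text begins "For young women and their families where there is no assumption of literacy", which fits questions being put orally. The part on mitigating risks covers stopping, taking a break, stepping out, a support telephone number, and safeguarding after a disclosure. It does not mention privacy from a companion.
- **Study objectives and Outcome measures.** A secondary objective is "To explore experiences, mentoring and thriving among young women receiving the 2YL intervention compared to those receiving usual care". Economic and social wellbeing and perspectives of thriving appear among the other secondary outcomes.
- **Background and rationale.** The protocol states that "pregnant teenagers are often neglected by their families" and adds that many have little protection from continuing gender-based violence.

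**The concern.** Depression and empowerment items are sensitive to who is listening. Here the listener may come from the household whose neglect the protocol gives as its reason for the scheme. The context table in the same subsection also raises child marriage and reluctant husbands, and the wording on companions does not exclude a husband.

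Two things are at stake. The first is the individual answer: an accompanied girl may under-report, or may disclose something in front of a person from whom she should be able to keep it. The second is the comparison between arms. If accompaniment shifts the scores and is more common in one arm, part of any difference reflects the interview setting. With presence unrecorded, nobody could examine this afterwards. The pilot exists partly to test data collection for a larger trial, so a weak procedure could be carried forward.

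**Working it through.** **1. Is there a figure to reproduce?** No. The protocol gives no SD, effect size, power or sample-size calculation for these scales. The check is therefore mainly a reading of the text, followed by a labelled illustration.

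**2. Does any text separate the scales from the joint format?** The choice of format applies to the interview as a whole, and the scales are given within the interview. I looked for a safeguard in the intervention description, Data collection and Ethical considerations. The intervention description asks for a setting where mentor and mentee can talk confidentially, but that concerns mentoring and not measurement. No text gives the scales in private, places them before the companion joins, allows self-completion, or records presence.

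**3. Could accompaniment differ by arm?** It is decided after randomisation. The scheme aims to re-establish family connections where that is safe, and mentors visit families to advocate for support. That could raise accompaniment under 2YL. The section on how the intervention may work also expects mentoring to build self-confidence and agency, which could make mentored girls more willing to be seen alone. A difference is plausible, but its sign is open.

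**4. Illustration.** The only input from the protocol is about 40 interviews. The rest is assumed: 20 per arm, independent observations with clustering ignored, a two-sided 5% test, a companion effect *s* (in SD) that is equal in both arms, and a between-arm difference *d* in the share accompanied.

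- Spurious arm difference = *s* × *d*.
- Standard error = √(2/20) = 0.316 SD.
- Difference detectable with 80% power = (1.960 + 0.842) × 0.3162 = 0.89 SD.
- False-positive rate = 1 − Φ(1.96 − *sd*/0.316) + Φ(−1.96 − *sd*/0.316).

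Spurious difference in SD, with the false-positive rate in brackets:

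| *s* | *d* = 0 | *d* = 0.2 | *d* = 0.4 | *d* = 0.6 |
|---|---|---|---|---|
| 0.2 | 0 (5.0%) | 0.04 (5.2%) | 0.08 (5.7%) | 0.12 (6.7%) |
| 0.5 | 0 (5.0%) | 0.10 (6.2%) | 0.20 (9.7%) | 0.30 (15.8%) |
| 0.8 | 0 (5.0%) | 0.16 (8.0%) | 0.32 (17.3%) | 0.48 (32.9%) |

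If *d* is negative the bias changes sign. If *d* is zero the arm difference is unbiased, although the scores of accompanied girls may still be shifted.

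In PHQ-9 points, assume an SD of 5, accompaniment of 60% against 30%, and 2 to 4 points under-reported when accompanied. The bias is 0.30 × 2 = 0.6 to 0.30 × 4 = 1.2 points. The standard error is 5 × √(2/20) = 1.58, so the bias is 0.6/1.58 = 0.38 to 1.2/1.58 = 0.76 of one standard error.

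**The case against.** A reader might infer that the scales are in fact read out in front of relatives, so that the answers partly measure the companion. The text does not say this. It is silent on when in the interview the scales are given, and the point could arise only for girls who choose the joint format. The girl may choose to be alone, she chooses her companion, and the invitation is twice made conditional on being appropriate. The distress and safeguarding provisions deal with part of the disclosure risk.

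A reader might also infer that 2YL would appear to improve mental health through the interview setting alone. The documents do not support that either. Accompaniment rates, under-reporting and SD are nowhere stated, the direction by arm is uncertain, and even the assumed PHQ-9 bias is below one standard error. The interviews cover about 40 girls who opt in individually at six weeks, the instruments are named only as examples, and the objective is exploratory with no test planned for these scales.

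Finally, the order of questions could be called interview-guide detail. That has some force. However, the protocol does fix the format and the mode of administration together. Its choice of format covers the whole interview, so a girl who wants support in the conversation is offered no private segment for the scales. What stands is the unprotected setting and the missing record of presence.

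**Conclusion.** The point holds as a weakness of procedure. As written, the plan permits depression, flourishing and empowerment scales to be completed with a family member or friend present, and it keeps no record of this. For accompanied girls that may reduce candour and raise a disclosure risk. It could also distort the exploratory comparison of wellbeing and thriving, but only if accompaniment, or its effect on scores, differs between arms. The table shows what could happen under assumed inputs and is not an estimate for this trial. The feasibility outcomes, the clinical composite and the power calculation do not depend on these scales. Severity is minor: a cheap improvement.

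**What to change.** In the Process Evaluation subsection of Data collection, state that:

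- the wellbeing scales are administered one-to-one, in private, before any companion joins;
- the one-to-two option remains for the qualitative conversation;
- for each scale, the interviewer records whether anyone else was present;
- presence is reported by arm alongside the scale results.

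The cost is a sentence or two in the protocol, a line in the interview guide, one recorded field and a few extra minutes per interview. Some girls may prefer company throughout. In that case the scales go ahead with the companion present and this is recorded, so some accompanied answers will remain but they can be identified.

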# Ethical considerations

Investigators will ensure that this study is conducted in accordance with the current principles of the Declaration of Helsinki (October 2008). The conduct of this study will be in full compliance with the relevant regulations and principles of Good Clinical Practice. The study will only start after gaining Institutional level consent and ethical approval from the local committee in Sierra Leone.

- **Primary and secondary clinical outcome data:** Primary outcome data will be collected individually, and we believe facility-based consent is appropriate considering the following, and will be requested from the ethics committee:

- The 2YL intervention is not a clinical intervention, is of minimal risk, and does not adversely affect the rights and welfare of the individual women.

- The intervention is delivered at the level of the trial area (cluster), rather than the level of the individual woman (the unit of randomisation is the trial area, not the individual woman)

- The requirement to seek consent from all young girls within each trial catchment area may make the trial unfeasible, particularly considering that individual woman will be unidentifiable by the research assistant at centralised data collection.

- **Process evaluation (including women’s experiences) data:** Informed written consent or thumb print will be sought by the research assistant for qualitative interviews and focus group discussions with healthcare workers, mentors and young women and their families. A pre-tested information sheet will be provided and discussed with participants and reasonable time (24 hours) will be given to consider this information before being asked to consent to participate. Potential participants will be asked whether they would like the information sheet to be read out or translated verbally into the local language (the recognised written language is English, and the information sheets will be in English; however, for verbal explanations, local languages will be used throughout).

**-** For the health workers focus groups, the research assistant will visit the PHUs, speak to the midwife in charge, and leave information sheets allowing a period of one week for potential participants to consider participation.

**-** For young women and their families where there is no assumption of literacy, a verbal explanation of the study will be provided in Krio or other local language, and give out information sheets which will be pre-tested. Consent will be sought at the start of all interviews and focus groups, with the information sheet being explained again, with opportunity for questions. For participants under 16, written consent will be sought from their parent or guardian where possible, using a personal approach by the research assistant to explain the research and the information sheet. Assent will be sought from the under 16-year-olds.

All participants being asked to provide personal sensitive data will be asked to give explicit consent for the collection and use of such data using the standard wording of the Data Protection Act statement. Participants will be fully informed on the Information Sheet of the intention to re-use or retain data for purposes other than the trial report, e.g. journal articles. Participants will be given the opportunity to withdraw from participation at any point both during the data collection and for up to four weeks following data collection.

Where eligible participants are present prior to a focus group starting (e.g., by a girl bringing an eligible friend along), consent will take place just prior to the focus group on the grounds that bringing the participant back on another occasion may disadvantage the participant economically or educationally.

Mitigating risks to participants

Talking about past abuses, bereavements or near-death experiences puts participants at risk of psychological stress or anxiety. To mitigate this risk, it will be clearly explained at the beginning of the focus group or interview that should the participant wish to stop the interview or step out of the focus group, that this is acceptable and that the research assistant can accompany them if they wish. If a participant becomes visibly upset, they will be encouraged to take a break from the interview or focus group. In both cases, their willingness to participate after a break should be reassessed. At the start of the interview or focus group, participants will be told that if they feel they would like some more support or an opportunity to talk in a safe place after the interview or focus group, they will be given a phone number to call to get help to arrange this. Young people may disclose illegal sexual activity - for example with a teacher or other adult in a pastoral role to the young person. In these situations, LNP safeguarding guidelines will be followed. In the case of disclosure of these and other harmful behaviours, details of various organisations offering specialist support will be offered to the participant.

Names and geographical locations will be removed from the transcription in order not to identify participants based on family or social group or address. If identification is still possible from other descriptive factors, these will be removed.

# Data analysis

# Sample size calculation

Sample size estimation has been provided by the trial statistician, [name], co-investigator and Reader in Medical Statistics, KCL. Based on experience with some of the proposed trial areas and global maternal health literature relevant to these settings^3,6^, we estimate the risk to adolescent pregnant women in Sierra Leone of experiencing a primary outcome (one of maternal death or stillbirth or neonatal death with no double counting) to be approximately 20% of all adolescent women. We also estimate a modest intra-cluster correlation of 0.02 (sites similar but not identical, and a simple exchangeable autocorrelation structure based on previous experience in Sierra Leone)^6^.

Prior to full proposal development, the 2YL team visited a typical peri-urban PHU similar in size and distance to referral hospital to trial sites. At least 16% of all deliveries among teens resulted in maternal death, stillbirth or early neonatal death. It was not possible to include late neonatal deaths up to 28 days. In addition, girls who were referred to a referral hospital in an emergency were not included in these numbers. We believe that this data can match the indicative estimate of 20% of girls experiencing a primary outcome.

This study is planned as a pilot, with main stated aim to demonstrate the feasibility of a fully powered study, and to help with its design. But for the purpose of the power calculation (intention to treat and not per protocol), an assumption of at least 42 deliveries per site has been made, with 20% having primary outcome composite events during the trial duration.  These numbers will provide 84% power to detect a 52% relative risk reduction (RRR) of the primary outcome (from 20% to 9%) assuming a models ICC 0.02.

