An initial evaluation of the 2YL intervention compared outcomes of young women pre-intervention (n=86) with those of other women post 2YL intervention (n= 67).^7^ In the 2YL cohort of young women who had mentors there were fewer maternal deaths (0% vs 10%) and lower levels of perinatal mortality (6% vs 16%), and infant mortality (11% vs 26%). Nearly all women receiving the 2YL intervention gave birth with a skilled birth attendant (SBA) and breastfed for longer than 6 months; and more than two thirds were using contraception by the baby’s first birthday, with no second pregnancies. In terms of fidelity of the intervention, mentors are required to provide at least one opportunity per week for a confidential 1:1 meeting, however most provided almost daily contact. All of the 2YL young women successfully ran a small business with support from their mentor, allowing them to learn business skills, eat well throughout pregnancy and provide for their baby. They reported increased self-confidence, supportive peer relationships, and a high level of satisfaction with the mentoring scheme. Subsequent anecdotal evidence is also now showing that the community engagement strategy pursued as an integral part of the early implementation is influencing more widely on ingrained attitudes towards practices which perpetuate gender inequality such as school non-attendance in pregnancy and child marriage.

Based on this preliminary data, the 2YL mentoring scheme is promising; it has potential to reduce maternal, neonatal and infant deaths rates, and sustainably improve livelihoods. However, a pilot trial is needed to assess the feasibility of recruitment, retention, collection of data and evaluation design. Such a trial and process evaluation should draw on the six core elements considered in the updated MRC framework for evaluating complex interventions which include: interacions between intervention and context, theoring how the intervention may work, diversity of stakeholders perspectives in research, uncertainainties, refinement of the intervention and resource and outcome consequences of the intervention.^8^

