Suboptimal maternal health care contributes to premature deaths, disability, and devastating spending in a country with an incipient financial crisis exacerbated by the 2014 Ebola epidemic (and further weakened during the ongoing COVID-19 epidemic). It has the highest maternal mortality rates in the world (1,360/100,000) with teens accounting for nearly 40% of all maternal deaths (more than two thirds caused by pre- eclampsia, haemorrhage and sepsis). Neonatal, infant and child mortality are also high (31.8, 83.5 and 11/1,000 respectively) and infants of mothers who die are up to 10 times more likely to die within their first 2 years. Antenatal attendance, access to skilled birth attendants and facility deliveries are low, and quality service delivery is often poor with disparities in access and availability to appropriate assessment and intervention, with delays in delivery, escalation of care and emergency maternity care.

Participants

Inclusion criteria

- Pregnant women aged under 18 at recruitment

Exclusion criteria

- There will be no exclusion criteria in terms of gestational age, as from an ethical and logistical standpoint, all young pregnant women should have access to the intervention, and pregnancy outcome data to be collected at an individual level.

Clusters and participant selection and enrolment

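### The 84% power rests on one asserted control risk of 20%, and the 12 listed clusters give about 75% at that risk with a two-sided 5% test

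*Protocol*

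**What the plan says.** In the protocol's Sample size calculation section, power is computed on one control risk, "with 20% having primary outcome composite events during the trial duration", for at least 42 deliveries per site. The section adds: "We also estimate a modest intra-cluster correlation of 0.02". The result is given as: "These numbers will provide 84% power to detect a 52% relative risk reduction (RRR) of the primary outcome (from 20% to 9"%). Alpha and sidedness are not stated.

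The support offered for 20% is general experience and literature, plus a visit to one peri-urban facility likened to the trial sites: "At least 16% of all deliveries among teens resulted in maternal death, stillbirth or early neonatal death". The section says that this count left out late neonatal deaths and girls referred in an emergency, and concludes: "We believe that this data can match the indicative estimate of 20% of girls experiencing a primary outcome".

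Other risk figures stand elsewhere in the protocol:
- Background and rationale: an evaluation that "compared outcomes of young women pre-intervention (n=86) with those of other women post 2YL intervention (n= 67"). The pre-intervention group had 10% maternal death and 16% perinatal mortality. The same section reports a survey with a maternal death rate of 1 in 10 among under-18s in Eastern Freetown.
- Background and rationale: "teenage mothers are 40-60% more likely to die during childbirth".
- Study design, setting and population: maternal mortality of 1,360 per 100,000, and "Neonatal, infant and child mortality are also high (31.8, 83.5 and 11/1,000 respectively"). No stillbirth rate is given.

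The number of clusters also varies. The design section, the flow chart and Appendix 1 have 12 areas (6 per arm). The Randomisation text speaks of sixteen areas and the intervention description of 8 intervention sites.

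**The concern.** For a fixed relative reduction, power depends mainly on the number of events, so it moves with the control risk. The plan fixes that risk at 20% and shows nothing on either side, although its own figures point to different values. Separately, the printed 84% should follow from the inputs printed beside it, and with 12 clusters and a conventional two-sided test it does not.

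The stake is how the pilot's between-arm result is read. A null result from a trial said to have 84% power would look like evidence against mentoring, when the actual power could be well below that. The figure also sits awkwardly with the protocol's health economics section, which says that pilot samples often have little or no power to detect differences between groups.

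**Working it through.** **Inputs.** Control risk 20%, intervention risk 9%, 42 per site and ICC 0.02 (Sample size calculation); 6 clusters per arm (12 areas, 1:1); 36 per PHU as the alternative size (participant selection section). Assumption: two-sided 5% test, z = 1.96.

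**Effect size.** 1 − 9/20 = 55%, not 52%. A 52% reduction from 20% would end at 9.6%. The 55% implied by the two printed risks is used below.

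**Method.** Design effect = 1 + (m − 1) × ICC. Effective n per arm = k × m / design effect. Power = Φ(d/SE − z), with SE = √{[p1(1 − p1) + p2(1 − p2)]/n}.

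**The plan's own figure, 12 clusters.**
- Design effect = 1 + 41 × 0.02 = 1.82; effective n = 252/1.82 = 138.5.
- SE = √[(0.16 + 0.0819)/138.5] = 0.0418; d/SE = 0.11/0.0418 = 2.63.
- Power = Φ(2.63 − 1.96) = 75% (74% with a pooled variance under the null).
- At 36 per site: design effect 1.70, effective n = 216/1.70 = 127.1, power 71%.
- At 9.6% instead of 9%, 42 per site: 69%.
- With a t reference on 10 degrees of freedom, which suits 12 clusters better, 20% against 9% gives about 66%.

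**What comes near 84%.**
- 8 clusters per arm, 42 per site, two-sided: effective n = 336/1.82 = 184.6, power 86% (85% pooled).
- 8 per arm, 36 per site, two-sided: 83% (82% pooled).
- 6 per arm, 42 per site, one-sided 5%: 84% (83% pooled).

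**Power by control risk, same 55% relative reduction, 42 per site, unpooled.**

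| Control risk | Intervention risk | Expected control events (6 × 42 = 252) | 6 per arm, two-sided | 8 per arm, two-sided | 6 per arm, one-sided |
|---|---|---|---|---|---|
| 26% | 11.7% | 66 | 87% | 95% | 93% |
| 20% | 9.0% | 50 | 75% | 86% | 84% |
| 16% | 7.2% | 40 | 64% | 76% | 75% |
| 12% | 5.4% | 30 | 50% | 62% | 62% |
| 10% | 4.5% | 25 | 43% | 54% | 55% |
| 8% | 3.6% | 20 | 35% | 44% | 47% |

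Whichever setting lies behind the 84%, moving from 20% to 16% costs 9 to 11 points.

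**What the protocol's inputs imply for the composite.**
- Facility visit: at least 16%. Its denominator is not given. If it were 42 deliveries (assumption), 7/42 has an exact 95% interval of 7% to 31%.
- Pre-intervention cohort (n=86): 16% if every maternal death coincided with a perinatal death, 16 + 10 = 26% if none did, before late neonatal deaths.
- National rates: maternal 1.36% × 1.4 to 1.6 = 1.9% to 2.2%; plus neonatal 3.18% = 5.1% to 5.4% for two of the three components. Reaching 20% would need about 15% from stillbirth.

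**The step from 16% to 20%.** Two omissions are named but neither is quantified. Late neonatal deaths cannot supply all four points at the national rate, since the whole neonatal rate is 3.18%. For referred girls, neither number nor outcome is given.

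**The case against.** The strongest reply is that 20% is reasonable. The 16% is a stated minimum with two named omissions, and girls referred in an emergency plausibly carry higher risk, so a value above 16% is no contradiction. The cohort range of 16% to 26% contains 20%, and so does the interval around 16% at the assumed denominator. The national rates are not specific to adolescents and omit stillbirth, and the protocol warns that maternal deaths are under-reported. The sites include Western Urban and Western Rural areas as well as rural districts. All of this stands.

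A reader might therefore infer too much in three ways. First, that the needed events are unlikely to occur: the documents do not show this, because no adolescent rate for the full composite in the trial areas is given. Second, that only the most favourable input was used, or that 20% is an upper limit: the cohort's 26% would have been more favourable. Third, that 84% is simply an arithmetical mistake: with alpha and sidedness unstated, a one-sided 5% test on 12 clusters reproduces it.

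It is also fair that feasibility is the main aim, and that reviewing the primary outcome and sample size for the larger trial is already an objective. It cannot be assumed that 20% would be carried forward unexamined. None of this supplies a derivation of 20%, a sensitivity range, or the test settings behind the 84%.

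**Conclusion.** The point holds in two parts. First, 20% is an asserted and untested planning value: 16% at one facility is compatible with it but does not confirm it, and the protocol's other figures leave wide room on both sides. Second, 84% does not follow from the 12 listed clusters under a two-sided 5% test; that design gives about 75% at 20% against 9%, or 71% at 36 per site. Over control risks of 10% to 26%, power runs from about 43% to 87%.

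These results assume a two-sided 5% test, a normal approximation, equal cluster sizes, ICC 0.02 and a constant 55% relative reduction. The values at 8% to 12% show sensitivity and are not predictions. Because this is a feasibility pilot, the matter is one of correct statement and interpretation and does not invalidate the design.

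**What to change.** In the Sample size calculation section:
- State alpha, sidedness and the actual number of clusters, and reconcile the 12 areas with the sixteen areas and 8 intervention sites mentioned elsewhere.
- Replace the single 84% with a short table of power, or expected confidence-interval width, over control risks of about 8% to 26%. Make the relative reduction agree with the two printed risks.
- Describe 20% as an uncertain planning value, neither an upper bound nor confirmed by the 16%.
- State that the between-arm comparison of the composite in this pilot is reported as an estimate with its interval, not as a powered test.

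The cost is a few sentences and one small table, with a less favourable stated power. No further sites or participants are needed.
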